# Enzalutamide versus flutamide for castration-resistant prostate cancer after combined androgen blockade therapy with bicalutamide: study protocol for a multicenter randomized phase II trial (the OCUU-CRPC study)

**DOI:** 10.1186/s12885-019-5526-3

**Published:** 2019-04-11

**Keywords:** Castration-resistant prostate cancer, Enzalutamide, Flutamide

## Abstract

**Background:**

Enzalutamide is an oral androgen receptor targeted agent that has been shown to improve survival in PREVAIL trials and has been approved for patients with chemo-naïve metastatic castration-resistant prostate cancer (CRPC). Meanwhile, flutamide is a non-steroidal oral anti-androgen that was commonly used before the approval of bicalutamide. The objective of the OCUU-CRPC study is to compare the efficacy and safety between second-line hormonal therapy of enzalutamide and flutamide as alternative anti-androgen therapy (AAT) after combined androgen blockade (CAB) therapy that included bicalutamide in patients with CRPC.

**Methods:**

A total of 100 patients with CRPC with or without distant metastases after disease progression who received CAB therapy with bicalutamide were randomly assigned at a 1:1 ratio according to distant metastases to the enzalutamide (160 mg/day, 4 × 40 mg capsules once daily) and flutamide (375 mg/day; 3 × 125 mg tablets thrice daily) groups. The primary endpoint for the drug efficacy is the response rate of prostate-specific antigen (PSA) (i.e., the ratio of patients whose PSA declined by ≥50% from baseline) at 3 months. Meanwhile, the secondary endpoints are PSA progression rate at 3 and 6 months, PSA response rate at 6 months, change in quality of life, PSA progression-free survival, and safety. The patient registration started in January 2015 and will end in March 2018, and the follow-up period is 6 months after the last patient registration. The main result will be reported in March 2019.

**Discussion:**

In the OCUU-CRPC study, we compare the efficacy and safety of enzalutamide or alternative AAT with flutamide in participants with CRPC who were previously treated with a CAB therapy with bicalutamide. The expected results of this study will be that enzalutamide is superior to flutamide in terms of PSA response. A longer time to disease progression with enzalutamide over flutamide may translate to better overall survival. However, flutamide may be more accessible for patients owing to its lower cost than enzalutamide.

**Trial registration:**

The OCUU-CRPC study was prospectively registered at clinicaltrials.gov (NCT02346578, January 2015) and University Hospital Medical Information Network (UMIN000016301, January 2015).

## Background

Prostate cancer is the most commonly diagnosed cancer and the third leading cause of cancer-related death among men worldwide [1]. In most patients who are treated for advanced recurrent prostate cancer with androgen-deprivation therapy (ADT) that comprise a luteinizing hormone-releasing hormone (LHRH) analogue or orchiectomy with or without an anti-androgen, disease progression occurs despite effective suppression of serum testosterone. These patients are then diagnosed with castration-resistant prostate cancer (CRPC).

In Japan, ADT has been widely used not only for advanced recurrent prostate cancer, but also for localized prostate cancer in elderly patients. Although ADT is effective only for a certain period and causes recurrence as CRPC, several patients actually respond to treatment for long periods [2]. Combined androgen blockade (CAB) therapy using an LHRH analogue with an anti-androgen is superior to ADT without an anti-androgen in terms of long-term efficacy among Japanese patients with prostate cancer [3]. Despite some disadvantages of CAB such as higher cost compared to ADT without anti-androgen, an observational study that compared CAB and castration showed good prognosis in patients with T1c-T3 prostate cancer [4]. At present, CAB using bicalutamide is more widely used in Japan than LHRH analogue monotherapy, and many elderly patients with localized prostate cancer are treated with CAB.

However, a proportion of patients with prostate cancer who are treated with CAB experience prostate-specific antigen (PSA) recurrence and are diagnosed as CRPC after confirming for anti-androgen withdrawal syndrome (AWS). Alternative anti-androgen therapy (AAT) with flutamide as the subsequent therapy after CAB therapy with bicalutamide is widely used before the androgen receptor targeted therapy (ART) era, particularly in Japan [5–11]. The response rate of AAT, defined as a decrease of > 50% from the baseline serum PSA level, was 22%, and patients who respond to AAT have been reported to have good prognosis [6]. This phenomenon is attributed to the different mechanism of actions among anti-androgens [9].

Flutamide, a non-steroidal oral anti-androgen, was often used in clinical practice before bicalutamide was approved. Some small, single-arm non-randomized studies suggest a PSA benefit in flutamide as second-line hormonal therapy [5–11]. However, the use of flutamide is optional for limited patients with CRPC according to the American Urological Association guidelines [12] owing to the modest PSA benefit, with PSA declines of > 50% occurring typically in only 20–40% of men with a median duration measured in several months.

Enzalutamide is an androgen receptor inhibitor that targets several steps in the androgen receptor signaling pathway. It inhibits binding of androgens to the androgen receptor, androgen-receptor nuclear translocation, and androgen receptor-mediated DNA binding [13]. In preclinical studies, enzalutamide showed a higher affinity for the androgen receptor and superior suppression of key components of the androgen receptor signaling pathway than bicalutamide [13, 14]. Subsequently, enzalutamide was approved for the treatment of metastatic CRPC based on the results of two pivotal placebo-controlled phase III trials, namely, AFFIRM [15] and PREVAIL [16].

Before the ART era, the treatment options for CRPC are limited, and AAT with flutamide has been widely used in Japan. However, no clinical studies compared AAT with flutamide and enzalutamide as treatment modalities for CRPC. Creating clinical evidence of the superiority of enzalutamide to AAT (bicalutamide to flutamide) in the post-AWS setting in terms of safety and efficacy would be meaningful. To the best of our knowledge, the OCUU-CRPC study is the first randomized head-to-head trial of enzalutamide versus flutamide in patients with CRPC after CAB therapy with bicalutamide.

## Methods/design

### Aim, design, and setting of the study

This study aims to compare the efficacy and safety of enzalutamide or AAT with flutamide in patients with CRPC who were previously treated with CAB therapy with bicalutamide. The efficacy and safety of enzalutamide and AAT with flutamide will be evaluated, and the effective therapy against CRPC after treatment with CAB therapy with bicalutamide will be investigated.

The present study is a phase II, investigator-initiated, multicenter, open-labeled randomized clinical trial of enzalutamide and AAT with flutamide in patients with CRPC after treatment with CAB therapy with bicalutamide. Patients will be randomized to receive treatment with either enzalutamide or flutamide, as shown in Fig. 1.

**Fig. 1 Fig1:**
[figure not shown]
The design of the OCUU-CRPC study

### Participant characteristics

#### Study population

The study population consists of 100 patients with CRPC who were previously treated with CAB with bicalutamide and whose serum testosterone level is less than 50 ng/dL (1.73 nmol/L) and have progressive disease after confirmation of AWS. Disease progression is defined as at least one of the following criteria: PSA progression, soft-tissue disease progression, or bone disease progression according to the Prostate Cancer Working Group 2 criteria [17].

#### Eligibility criteria

The inclusion criteria are as follows:Serum testosterone of less than 50 ng/dLDisease progression diagnosed on imaging or PSA progression (i.e., consecutive increase of all PSA values measured at least thrice at a 1-week interval and a final value of 2 ng/mL or more. If the third value is not higher than the second one, a fourth measurement will be taken and its value must be higher than the second one in order for the patient to qualify)Disease progression after CAB with bicalutamideEastern Cooperative Oncology Group performance status (PS) of 0 or 1Age 20 years or olderWritten informed consent

The exclusion criteria are as follows:Any prior treatment with enzalutamide, flutamide, abiraterone, or chemotherapy, except for neoadjuvant therapyPresence of active double cancerAny prior treatment with bicalutamide within 6 weeksSystemic biological therapy (except for existing approved drug as bone-modifying agents or treatment with LHRH analogues) or treatment with other antitumor agents for prostate cancerPresence of severe complicationsHistory of hypersensitivity to enzalutamide or any other excipient of enzalutamideHistory of hypersensitivity to flutamide-containing agentLiver dysfunctionParticipants who are considered as ineligible by the investigator

#### Methods of recruitment and random allocation

Patient recruitment started in January 2015 and is targeted to end by March 2018. Eligible patients are randomly assigned to one of the two treatment groups through the data center at DOT International Inc. (which was responsible for data entry, coding, security, and storage, including any related processes to promote data quality). Patients will be randomly allocated to the enzalutamide or flutamide group via dynamic allocation using metastatic condition (M0, M1) and baseline PSA level as prognostic factors.

#### Treatment

Patients were randomly assigned at a 1:1 ratio to the enzalutamide (160 mg/day, 4 × 40 mg capsules once daily) or the flutamide (375 mg/day; 3 × 125 mg tablets thrice daily) group according to disease stage (M0 or M1). M0 means the absence of bone metastases on bone scan and of soft-tissue disease, while M1 means bone metastases on bone scan or soft-tissue metastases including nodal involvement above the aortic bifurcation. Both treatments are performed within the coverage of the National Health Insurance privilege of the patients. If the patients satisfy the criteria defined below for changing the drug, the initial medication used will be discontinued. The subsequent medication is not specified, and the investigator will choose the appropriate treatment option based on the patient condition. Enzalutamide is expected to be the primary drug for the subsequent treatment of patients in the flutamide group.

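### The flutamide regimen does not agree with itself in its ordinary reading: the tablet schedule gives 1125 mg/day beside a stated total of 375 mg/day

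*Protocol article*

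**What the plan says.** The Treatment section of the protocol article states the control regimen as "375 mg/day; 3 × 125 mg tablets thrice daily". The Methods paragraph of the abstract gives the same figures: "flutamide (375 mg/day; 3 × 125 mg tablets thrice daily) groups". In both places the other arm is described in a similar pattern; in the Treatment section it reads "160 mg/day, 4 × 40 mg capsules once daily".

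These are the only two statements of the flutamide dose in the article. No section gives the number of tablets per intake or per day in any other form.

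**The concern.** Each regimen entry has three parts: a daily total, a number of units with their strength, and a frequency. The parts should multiply out to the total. For flutamide, read in the ordinary way, they do not. A reader who follows the tablet schedule and a reader who follows the daily total arrive at amounts that differ by a factor of three.

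Flutamide is the randomized comparator. The primary endpoint (Endpoints of the study) is the PSA response rate at 3 months, and adverse events are a secondary endpoint. Both are compared against the flutamide arm. A result against a control whose regimen can be read in two ways is hard to interpret or reproduce. It is also a safety matter for anyone who takes the tablet instruction from the published text.

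**Working it through.** **Inputs** (all from the Treatment section; the abstract gives the same figures)

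- Enzalutamide: stated total 160 mg/day; 4 capsules of 40 mg; once daily.
- Flutamide: stated total 375 mg/day; 3 tablets of 125 mg; three times daily.

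**Reading A, count per intake.** Daily dose = units per intake × strength × intakes per day.

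- Enzalutamide: 4 × 40 × 1 = 160 mg/day. This matches the stated total.
- Flutamide: 3 × 125 × 3 = 1125 mg/day, from 3 × 3 = 9 tablets a day. This does not match 375 mg/day; the ratio is 1125 / 375 = 3.0.

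**Reading B, count per day.** Daily dose = units per day × strength, and the frequency only says how they are spread.

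- Enzalutamide: 4 × 40 = 160 mg/day. This matches.
- Flutamide: 3 × 125 = 375 mg/day, taken as one tablet at each of three intakes (1 × 125 × 3 = 375). This matches.

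| Entry | Stated total | Reading A | Reading B |
|---|---|---|---|
| Enzalutamide | 160 mg/day | 160 mg/day | 160 mg/day |
| Flutamide | 375 mg/day | 1125 mg/day | 375 mg/day |

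**Does the enzalutamide entry settle the notation?** No. At one intake a day, the count per intake and the count per day are the same number. The entry gives 160 mg/day under both readings and cannot discriminate between them.

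**Does the wording settle it?** Not fully. In "3 × 125 mg tablets thrice daily" the frequency directly follows the tablets, so the ordinary sense is three tablets on each of three occasions, which is Reading A. The stated total supports Reading B. The two parts of one parenthesis therefore point in different directions, and nothing elsewhere in the article decides between them.

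**Does anything in the design depend on it?** The section on the target sample size uses response rates, power, alpha and a dropout rate. No dose enters, so those figures are unaffected either way.

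**The case against.** The strongest reply is that Reading B makes both entries agree with their own totals, while Reading A fails for one of them. On that view the phrase is loose shorthand rather than an error: the daily total is explicit, it is the same in both places, and no other total appears. This largely stands. It shows that an innocent explanation exists and that the enzalutamide entry cannot be used to prove Reading A. It does not make the phrase clear, because Reading B requires the frequency to be read as not multiplying the tablets it follows, and the article never says that.

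A second reply is that this is a journal article condensing a fuller protocol. That would excuse leaving the regimen out. It does not cover a regimen that is printed twice with figures that disagree in their ordinary reading.

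A reader might also infer that sites followed different readings, so that the control arm mixed two regimens and patients were exposed to harm. The documents do not support this. Nothing in the article shows how flutamide was dispensed or that dosing varied. The exclusion for liver dysfunction and the rule on changing drug for adverse effects say nothing about dose, so they are no evidence of it.

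Nor would a notice to sites be likely to do much now. Registration was planned to end in March 2018, follow-up was to run 6 months after the last registration, and the article appeared on 11 April 2019.

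**Conclusion.** The point holds as an internal inconsistency in the wording of the control regimen. In its ordinary reading the tablet schedule gives 1125 mg/day, which is 3.0 times the 375 mg/day printed beside it. The conflict disappears only if the tablet count is a daily count, which the text neither states nor excludes.

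This conclusion rests on the printed words and on multiplication; no outside figure is used. It does not establish which figure was intended, and it does not show that any patient received a regimen other than the one planned. The planned sample size and power stand or fall on other grounds.

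It still deserves correction because it concerns the operative description of the comparator, and because the discrepancy is threefold and appears in the abstract as well as in the body.

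**What to change.** Reconcile the daily total, the number of tablets per intake and the number of intakes per day against the full protocol. Then state the three so that they multiply out in only one way, in both the Treatment section and the abstract. Writing the tablets per intake separately from the tablets per day would remove the ambiguity. Which figures are correct is for the sponsor to establish; none is proposed here.

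In the results report, describe the flutamide regimen actually given, checked against prescribing or dispensing records.

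The cost is a wording correction in two places and a records check. No design parameter or analysis changes.

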#### Criteria for changing the drug

The treatment will be changed in case of the following conditions:Disease progression, as defined below (either of one)PSA progression: Three consecutive increases in PSA, an increase of ≥25%, and an absolute increase of ≥2 ng/mL above baselineDisease progression as noted on radiographyWorsening of symptomsAdverse effects that cause difficulty in continuing the medication

#### Discontinuation of the treatment

The investigator will discontinue the treatment or the study and record the reasons for such when the following conditions occur:Patient withdraws from the studyPatient diedPatient cannot continue the treatment because of hospital transferThe patient was found to be ineligible for the studyAny other cases where the investigator determines that the treatment can be discontinued

#### Endpoints of the study

The primary endpoint of the study is a PSA response rate (i.e., the ratio of patients whose PSA decreased by ≥50% from baseline) at 3 months. Meanwhile, the secondary endpoints in the OCUU-CRPC study are as follows:PSA progression rate at 3 monthsPSA response rate at 6 months: If initial enzalutamide therapy is switched to other treatments due to disease progression before 6 months, such cases are regarded as “non-responders” regardless of the efficacy of the subsequent treatment. In addition, the PSA response rate in patients in whom flutamide is switched to enzalutamide will be calculated to determine the efficacy of enzalutamide in the flutamide to enzalutamide cohort.PSA progression rate at 6 monthsChange in quality of life (QOL) as assessed using the Functional Assessment of Cancer Therapy-Prostate (FACT-P) scale in JapanesePSA progression-free survival that is calculated for the initial drug in each armAdverse events (AEs)

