#### Items to record and schedule

Patient information during initial diagnosis of prostate cancer including the following:date of birth, diagnosis date, age, PSA level, Gleason score, clinical stage, metastatic sites, and rate of bone metastasesPatient information during registration (Table. 1):Patient background data: institution ID, registration date, date of birth, age, height, body weight, PS, concomitant disease, blood sampling (PSA, serum testosterone, white blood cell (WBC), red blood cell (RBC), alkaline phosphatase (ALP), and lactate dehydrogenase (LDH), among others)Imaging: computed tomography (CT) and bone scintigraphy shall be performed on registration to verify metastatic sitesQOL (FACT-P)Follow-up after registration (Table. 1);Blood sampling (PSA, WBC, RBC, ALP, and LDH, among others): every monthAEs as classified according to the CTCAE ver. 4.0: every monthImaging test: CT and bone scintigraphy when progressive disease is suspectedQOL (FACT-P): every 3 months

**Table 1 Tab1:** Follow-up schedule of examination

	Baseline	1 month	2 months	3 months	Every 1 month	Every 3 months	Discontinuation of therapy
Informed consent	○						
Medical history	○						
Confirmation of eligibility criteria	○						
Randomization	○						
Serum testosterone	○						
FACT-P	○	–	–	○	–	○	○
PSA^a^	○	○	○	○	○	○	○
Biochemical examination^a^	○	○	○	○	○	○	○
CT, bone scintigraphy	○	When progressive disease is suspected^b^					○
Safety	○	○	○	○	○	○	○
Further therapy	–	–	–	Best standard care			

^a^After the discontinuation of enzalutamide or flutamide, PSA and biochemical examination will be continued until September 2018

^b^When progressive disease is suspected, CT and bone scintigraphy will be performed to confirm radiographic disease progression

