### Calculation of the target sample size

We hypothesize that the PSA response rate (PSA reduction by ≥50%) of enzalutamide at 3 months is 75%. According to the PREVAIL study [16], the best PSA response rate was 78%. Moreover, most patients in that study achieved a ≥ 50% PSA response at 3 months. Therefore, we can assume 75% as the PSA response rate at 3 months in the enzalutamide arm. On the other hand, the PSA response rate of flutamide is 35% [9]. The primary efficacy endpoint is PSA response rate at 3 months after the initial treatment. A total of 41 patients per group will provide an 90% power to detect an absolute difference in response rate of 50% (75% vs. 25%) at 2-sided α of 0.05 for superiority test with 5% margin. A dropout rate of 10% is expected; thus, *N* = 50 per group is considered to be adequate.

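### The 6-month PSA response rule makes switchers for progression non-responders in the enzalutamide arm only and leaves flutamide switchers without a rule

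*Protocol article*

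**What the plan says.** All references are to the protocol article.

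- **Endpoints of the study.** PSA response at 6 months is a secondary endpoint. Its only rule on switching reads: "If initial enzalutamide therapy is switched to other treatments due to disease progression before 6 months, such cases are regarded as" non-responders. What the next drug achieves is set aside for these patients ("regardless of the efficacy of the subsequent treatment"). The rule names one arm and one reason for switching.
- **Same section, on flutamide switchers.** As an addition, "the PSA response rate in patients in whom flutamide is switched to enzalutamide will be calculated to determine the efficacy of enzalutamide" in that cohort. How these patients score in the flutamide arm's own 6-month rate is not said.
- **Same section, for contrast.** PSA progression-free survival is tied to the initial drug in both arms.
- **Treatment.** "Enzalutamide is expected to be the primary drug for the subsequent treatment of patients in the flutamide group".
- **Items to record and schedule, Table 1, footnote a.** "After the discontinuation of enzalutamide or flutamide, PSA and biochemical examination will be continued until September 2018".
- **Criteria for changing the drug.** Besides disease progression, worsening symptoms and adverse effects are also grounds for a change. The 6-month rule mentions neither.

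**The concern.** A rule for treatment switching decides what a 6-month response rate measures. Here the rule is written for one arm. An enzalutamide patient who progresses and changes drug is fixed as a failure. A flutamide patient who progresses and changes drug has no stated score, will usually be taking the comparator drug, and will have a month-6 PSA value on file. An analyst who applies the text as written could count that value, and a decline produced by enzalutamide would then be credited to the flutamide arm.

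The comparison would then lean one way: the flutamide rate goes up and the difference goes down. A second, smaller gap is that a switch for toxicity or worsening symptoms has no stated score in either arm.

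**Working it through.** **Is there a figure to reproduce?** No. The article gives no rate, power or sample size for 6-month response, so the check is a reading of the rule plus an illustration of size.

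**Can the gap be exercised in practice?** PSA is measured monthly, and PSA progression needs three consecutive increases, among other conditions. A patient whose PSA rises from the start can qualify at month 3 and then has up to 3 months on the next drug before the 6-month assessment. The sample size section says most patients in the cited placebo-controlled enzalutamide trial who were to respond had done so by 3 months. A rescue response by month 6 is therefore possible.

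**Inputs**

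- pE, enzalutamide rate: 75%, from "we can assume 75% as the PSA response rate at 3 months in the enzalutamide arm". This is a 3-month figure, used here as a stand-in for 6 months.
- pF, response on flutamide: the sample size section gives two values. One sentence has "the PSA response rate of flutamide is 35"%. The power statement uses an "absolute difference in response rate of 50% (75% vs. 25"%). Both are carried.
- r, response after switching to enzalutamide: 60.7% (17 of 28 Japanese patients, most previously given both bicalutamide and flutamide; Discussion) up to the 75% design rate.
- s, share of the flutamide arm that has not responded on flutamide and switches in time: not in the documents. **Assumption: 20% to 40%.**

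**Formula.** If rescued patients are counted, the flutamide rate is pF + s × r. The difference shrinks by s × r, whatever pE is.

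| s | r | s × r | Counted rate, pF 25% | Difference from 75% | Counted rate, pF 35% | Difference from 75% |
|---|---|---|---|---|---|---|
| 0.20 | 0.607 | 12.1 | 37.1% | 37.9 | 47.1% | 27.9 |
| 0.20 | 0.75 | 15.0 | 40.0% | 35.0 | 50.0% | 25.0 |
| 0.40 | 0.607 | 24.3 | 49.3% | 25.7 | 59.3% | 15.7 |
| 0.40 | 0.75 | 30.0 | 55.0% | 20.0 | 65.0% | 10.0 |

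With switchers scored as non-responders in both arms, the flutamide rate stays at pF and the difference is 75 − 25 = 50 or 75 − 35 = 40 points.

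**Why the true rise is probably smaller.** A patient who switches for PSA progression is at least 25% above the study baseline. To count as a responder against that baseline, PSA must fall from at least 1.25 to 0.50 of baseline, which is a fall of at least 1 − 0.50/1.25 = 60% from the switch value, within about 3 months. The 60.7% and 75% figures describe enzalutamide response from the patient's own pre-enzalutamide baseline, so they are generous for r.

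**The case against.** The strongest reply is that silence is not bias. The article never says that PSA after a switch counts for flutamide. The separate flutamide-to-enzalutamide analysis is described as measuring the efficacy of enzalutamide, which suggests that the authors meant to keep those patients apart. Tying PSA progression-free survival to the initial drug points the same way. An incompletely written rule is at least as plausible as a decision to credit rescue to flutamide.

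This stands as far as intention goes. A reader might infer that the endpoint has become enzalutamide alone against flutamide followed by enzalutamide, and so no longer compares the two drugs. The documents do not support that: they permit such scoring but do not order it. Nor does the reply close the gap. The cohort analysis is an addition and does not make those patients non-responders in the arm comparison.

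A second reply concerns weight, and it also stands. This is one of several secondary endpoints in a phase II trial, and the sample size rests on 3-month response alone. Any bias would run against the result the authors expect, so it could not manufacture a finding that enzalutamide is superior.

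It could also be said that an article may leave scoring to the full protocol or analysis plan. Here, though, the article does state the scoring rule, and states it for one arm.

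**Conclusion.** The point holds in a limited form and should be fixed. The 6-month response rule covers one arm and one reason for switching. Applied literally, it lets the arms be scored differently, in a direction that raises the flutamide rate.

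The size is illustrative: about 12 to 30 points, against a design difference of 50 or 40 points, and probably less for the reasons shown. It rests on the assumed switch share, on borrowed rescue rates, and on switchers not already being counted as flutamide responders. A patient who responded on flutamide and then switched for toxicity would otherwise be counted twice.

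Three stronger readings are tempting but not supported:

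- **A rise of up to 45 points.** This needs 60% switched and 75% responding (0.60 × 0.75). It multiplies two assumed extremes.
- **A planned difference of simply 40 points.** The power statement says 50; the 40 follows only from the 35% flutamide rate given beside it.
- **Any stop of the initial drug must count as non-response.** That is a choice of estimand, not a correction the text compels. It would also turn hospital transfers and patients found ineligible (Discontinuation of the treatment) into drug failures.

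**What to change.** Replace the one-arm sentence with a rule for both arms: a patient in either arm whose initial drug is switched because of disease progression before 6 months is a non-responder for that drug, whatever the later PSA. Keep the flutamide-to-enzalutamide cohort as a separate descriptive analysis.

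Add that switches for adverse effects or worsening symptoms are scored identically in both arms, and that PSA after a switch is never credited to the initial drug. Report PSA regardless of switching as a sensitivity analysis, scored the same way in both arms.

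The 6-month PSA progression rate is not settled by this wording. Setting aside post-switch PSA does not say whether a patient who stopped for toxicity counts as progressed, so that endpoint would need its own statement.

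The cost is a few sentences and one extra analysis. No new data are needed and patient management does not change. The small downside is that some patients who stop for reasons other than progression may count as failures; the sensitivity analysis shows how much that matters. As the trial is open-label, the rule should be fixed before the 6-month results are analysed.
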